### Study procedure

This study consists of two phases including (i) a baseline phase (week 0) and (ii) a 6-week treatment phase (week 1 to week 6).

Once potential participants show interest in this trial, they will be invited to attend an eligibility assessment in which their eligibility will be assessed by trial investigators; thereafter, eligible participants will be enrolled and randomly assigned to either the fire needle group or the filiform needle group and given a 6-week treatment.

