### Randomization and allocation concealment

The randomization will be performed by the Research Centre of Clinical Epidemiology, Peking University Third Hospital. A block randomization method will be used to generate the random allocation sequence; predetermined computer-generalized randomization opaque sealed envelopes will be used to ensure the allocation concealment. The opaque sealed envelopes, with the participant’s screening order printed outside and randomly assigned group printed inside, will be numbered consecutively and connected into a strain. Researchers will enroll the eligible participants after screening, then separate and open each envelope from the strain in the sequence corresponding to the participant’s screening order and assign the eligible participant into either the fire needle group or filiform needle group.

The statistician who generates the randomly assigned sequence is not the same person as the researcher who decides whether the subject is qualified. People who generate or save the randomly assigned sequence cannot participate in the trial process.

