### Blinding

Outcome assessors and personnel involved in data collection and data analysis will be blinded to participants’ group allocation throughout the entire trial. The acupuncturist and participants cannot be blinded due to the nature of the intervention, but they will be informed not to communicate with outcome assessors regarding treatment procedures and responses.

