### Outcome measures

The efficacy of the treated patients will be evaluated before treatment and 6 weeks after intervention. The main efficacy indicator is the WOMAC questionnaire for knee pain, stiffness, and function. The secondary efficacy outcomes are VAS for generalized pain and SF-12 for quality of life. The collected information and data will be maintained confidentially.

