### Statistical analysis

Using the statistical software of SPSS 20.0, *p* < 0.05 for a two-sided test will be regarded as the standard to judge the significance of the difference. The measurement data will be expressed as mean ± standard deviation ($$ \overline{x} $$ ± *s*). If the precondition of a parametric test is satisfied, *t* test will be chosen. For non-parametric data, a Wilcoxon rank sum test will be used. The counting data will be expressed as frequency (or rate), which is calculated by a chi-square test or Fisher’s exact test.

The results of the study will be statistically analyzed according to the principle of intention-to-treat (ITT) and per-protocol population (PP). In ITT, all enrolled participants who have treated at least once will be analyzed. In PP, all participants who meet the study criteria, have completed the observation, have good compliance, do not use prohibited drugs during the study, and completed the study contents will be analyzed. Finally, comparison of the consistency of the results between ITT and PP will be conducted. The multiple imputation method will be used to process the missing data for the primary outcome.

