This study will compare the clinical efficacy for treating knee osteoarthritis between fire needle and filiform needle acupuncture, so the subjects will be randomly allocated to the fire needle group or the filiform needle group. It is difficult to have a placebo control group with no acupuncture treatment, since the subjects who come to the acupuncture and moxibustion departments are all expecting acupuncture treatment. At present, there are generally two methods for placebo control of sham needle or acupuncturing non-acupoint points which are not related to the treatment or not inserting into the subcutaneous area. However, both two methods are questionable and remain to be discussed [3, 29, 30], so the sham needle group will not be set up in this study.

This study is a prospective randomized controlled trial, using randomization and allocation concealment to decrease selection bias and using blinding method to reduce information bias. However, it is difficult to be double-blinded in practice because both doctors and subjects can see and feel the difference between fire needle acupuncture and filiform needle acupuncture, especially Chinese people, who are particularly familiar with acupuncture and moxibustion. Therefore, only the third-party evaluator will be blinded in this study.

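### The set labelled ITT leaves out randomised participants who never start treatment, so in this unblinded trial the main comparison may not be as randomised

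*Protocol article*

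**What the plan says.** The Statistical analysis section names intention-to-treat and per-protocol as the two bases for analysis. It then fixes the first set: "In ITT, all enrolled participants who have treated at least once will be analyzed". The per-protocol set is narrower, requiring eligibility, completion, good compliance and no prohibited drugs. The section ends with a cross-check, "Finally, comparison of the consistency of the results between ITT and PP will be conducted", and with multiple imputation for missing primary outcome data.

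Three other places bear on who can fall outside the set:

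- **Order of events.** Under Study procedure, "eligible participants will be enrolled and randomly assigned to either the fire needle group or the filiform needle group", and the 6-week treatment follows. Under Randomization and allocation concealment, "Researchers will enroll the eligible participants after screening, then separate and open each envelope from the strain".
- **Blinding.** "The acupuncturist and participants cannot be blinded due to the nature of the intervention". The Discussion adds that "both doctors and subjects can see and feel the difference between fire needle acupuncture and filiform needle acupuncture".
- **Assessment.** Under Outcome measures, "The efficacy of the treated patients will be evaluated before treatment and 6 weeks after intervention".

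**The concern.** Intention-to-treat means that everyone randomised is analysed in the arm assigned, whether or not treatment began. Requiring at least one session makes membership depend on something that happens after randomisation. This restriction is easiest to defend when the decision to start cannot be influenced by knowing the allocation. Here it can be: treatment is open, and one arm uses needles heated until red while the other uses ordinary filiform needles. Willingness to start may depend on the arm and on patient characteristics such as pain severity or expectation, which also predict WOMAC.

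If some participants decline at that point, the groups compared are no longer the groups that randomisation formed. The Discussion relies on randomisation and concealment to limit selection bias, and an exclusion applied after the envelope is opened can let that bias back in. The article states this definition outright, so it is not a detail left to an analysis plan that is not shown.

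**Working it through.** The plan gives no figure on this point to reproduce. The check is a reading of the sections together, followed by an illustration on assumed inputs.

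**Can a randomised participant fall outside every efficacy set?**

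1. Study procedure puts enrolment and assignment before treatment, and the randomisation section has the envelope opened after enrolment. A person can therefore be randomised and receive no session.
2. The ITT definition excludes that person.
3. The per-protocol set requires completion and good compliance, so it excludes that person too.
4. The imputation rule fills in missing outcomes for people in an analysis set. It does not bring back people whom the definition has removed.
5. No other section brings them back.

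Both sets thus omit the same people, and comparing the two cannot show the effect of omitting them.

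**How large could the shift be?** Suppose k of the n = 50 randomised to one arm never start, and their mean outcome would differ by D from the mean m of those who do. Then

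- mean of all randomised = [(50 − k)·m + k·(m + D)] / 50 = m + k·D/50
- mean of the set as defined = m
- size of the shift from exclusion = k·D/50

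Inputs from the Sample size calculation section: SDs 20.85 and 23.80, MCID 6.7, 50 per group.

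- Pooled SD = √[(20.85² + 23.80²)/2] = √500.58 = 22.37
- 0.25 SD = 5.59 points; 0.5 SD = 11.19 points

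Assumed, because the article gives no values: k and D, and no never-starters in the other arm.

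| k of 50 | D | Shift (WOMAC points) | Share of 6.7 |
|---|---|---|---|
| 0 | any | 0 | 0% |
| 3 | 0.25 SD | 3/50 × 5.59 = 0.34 | 5% |
| 5 | 0.5 SD | 5/50 × 11.19 = 1.12 | 17% |
| 7 | 0.5 SD | 7/50 × 11.19 = 1.57 | 23% |

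A wider grid gives the same order of size. With k = 1 to 5 and D = 5 to 20 points, the shift runs from 1/50 × 5 = 0.1 to 5/50 × 20 = 2.0 points. If the whole planned 20% loss in one arm (k = 10) were never-starters, it runs from 10/50 × 5 = 1.0 to 10/50 × 20 = 4.0 points. The article does not say when that loss is expected.

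**Against sampling error.** With 50 per group, the standard error of the contrast is 22.37 × √(2/50) = 4.47 points. The 1.12-point case is 1.12/4.47 = 0.25 of a standard error, and the 1.57-point case is 0.35.

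**Two limits.** The SDs describe scores after treatment, whereas the abstract defines the primary outcome as change in WOMAC, whose SD is not given. If both arms lose people, the net shift is the difference between the two arms' k·D/50 terms, which may partly cancel or may add.

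**The case against.** The strongest reply is that the harm is conditional and probably modest. Participants give written consent, are interviewed and told the study details, and, according to the Discussion, come expecting acupuncture. Few may refuse, and if nobody does, the set as defined is identical to true ITT. Even the assumed cases above are well below one standard error. This stands, and it limits how serious the point is. It does not make the definition right.

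Several stronger readings are tempting, but the article does not support them:

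- **That only the fire needle arm would lose people.** The rule applies to both arms, and some assigned to filiform needles might decline because they hoped for the other treatment. Which arm would lose more is not documented.
- **That participants certainly learn their arm when the envelope is opened.** The researcher opens it. When the participant is told, and how long before the first session, is not stated. Disclosure before treatment is plausible given the sequence and the lack of blinding.
- **That ITT and per-protocol have been given equal standing.** The section lists both and plans a consistency check. Not ranking them is silence in a condensed article, and a ranking may stand elsewhere.
- **That agreement between the two sets is worthless.** The ITT set keeps those who stop, comply poorly or are lost after the first session, and the per-protocol set removes them. Agreement is informative about those events. It is uninformative only about never-starters.
- **That the Outcome measures section rules out assessing untreated participants.** Its reference to treated patients reads as general wording and is weak support at most.

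**Conclusion.** The point holds in a limited form. The article claims intention-to-treat but defines a modified ITT set. With assignment before treatment and no blinding of participants, people who decline after learning their arm would be left out of both efficacy sets, and the planned comparison of those sets cannot detect it.

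The size and direction of any bias cannot be derived from the article. The illustrated 0.3 to 1.6 points rests on an assumed 3 to 7 never-starters in one arm, an assumed difference of 0.25 to 0.5 SD, and an SD taken from post-treatment scores. It is zero if everyone starts. A reader might infer that the trial's conclusion is compromised; the arithmetic does not show that. This should be fixed because the stated rule is wrong and cheap to correct, but it is not a defect that by itself invalidates the plan.

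**What to change.** - Define ITT as all randomised participants, analysed in the arm assigned whether or not any session was given.
- Seek the week-6 WOMAC from everyone, including those who never start.
- Extend the planned multiple imputation to never-starters whose week-6 score is still missing. State that imputation corrects only differences explained by the variables in the imputation model. If never-starters differ in ways those variables do not capture, only collected outcomes will help, so follow-up matters more than the wording.
- Keep the treated-at-least-once set, labelled modified ITT, as a sensitivity analysis.
- Report the number of never-starters by arm, with reasons where known.

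The cost is a change of wording and a few extra questionnaire contacts. It needs no additional participants and no change to treatment. It should be settled before outcomes are examined by arm, so that the choice of set cannot appear to follow the data.

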### Ethics and dissemination

This study will adhere to the principles of the *Declaration of Helsinki (2008)*, *Measures for the Ethical Review of Biomedical Research Involving Humans (2007)* issued by the Ministry of Health, and *Administrative Regulations on the Ethical Review of TCM clinical research (2010)* issued by State Administration of Traditional Chinese Medicine of the People’s Republic of China, and it has been approved by the Research Ethics Committee of Beijing Hospital of Traditional Chinese Medicine, Capital Medical University, on 8 June 2018 (reference 2018SB-066). The study has been registered with the Chinese Clinical Trial Registry (ChiCTR) on 18 November 2018, and the registration number is ChiCTR1800019579. The results will be disseminated through publications in open source scientific peer-reviewed journals, presentations in scientific conferences, or a master’s thesis. The identifying images or other personal or clinical details of participants that compromise anonymity will not be published.

## Discussion

As a chronic degenerative disease, osteoarthritis involves younger patients with a high incidence and substantial long-term disability rate. Joint pain and limitation of motion in osteoarthritis subjects lead to decreased muscle strength, changes in the biomechanical axis, and disuse atrophy of the muscle, resulting in changes in the function of the lower limbs, changes in joint stress distribution, and decreased joint stability, entering a vicious cycle [22]. At present, there are limitations of medical and other treatment methods [3], which makes the advantages of acupuncture more prominent. This study will evaluate the efficacy and safety of fire needle and ordinary filiform needle acupuncture for knee osteoarthritis by clinically comparative observation, which lays a foundation for subsequent large-scale multi-center randomized controlled trials. It may also contribute to the optimization of the clinical treatment plan for knee osteoarthritis with fire needle and the internationalization of fire needle therapy.

Acupuncture is popular in China due to its long history, simple operation, good efficacy, low cost, relative safety, and other advantages, and has been demanded as a complementary and alternative medicine by more and more subjects all over the world. As a special kind of acupuncture, it is believed in TCM to spell out that fire needle acupuncture has the dual effects of dredging the meridian through stabbing and dissipating cold through the heat, which can enhance the circulation of blood and qi. Osteoarthritis is one of the diseases recommended by the World Health Organization to be treated with acupuncture and moxibustion [23]. Studies have shown that broil stimulation can dilate the blood vessels in the affected parts, improve the osmotic pressure, stimulate the stress response of the body, and promote self-repair ability [24]; inhibit the local immune response and eliminate joint swelling and stiffness to relieve pain [25]; promote the formation of benign self-regulation mechanism, cell growth factors including vascular endothelial growth factor (VEGF), promote the growth of granulation tissue, and accelerate the closure of wounds [26], so as to relax the muscles and tendons, nourish the joints, and relieve pain. The selection of acupoints is based on the acupuncture theory of TCM, decades of clinical experience in our department, and systematic reviews [27, 28].

This study will compare the clinical efficacy for treating knee osteoarthritis between fire needle and filiform needle acupuncture, so the subjects will be randomly allocated to the fire needle group or the filiform needle group. It is difficult to have a placebo control group with no acupuncture treatment, since the subjects who come to the acupuncture and moxibustion departments are all expecting acupuncture treatment. At present, there are generally two methods for placebo control of sham needle or acupuncturing non-acupoint points which are not related to the treatment or not inserting into the subcutaneous area. However, both two methods are questionable and remain to be discussed [3, 29, 30], so the sham needle group will not be set up in this study.

This study is a prospective randomized controlled trial, using randomization and allocation concealment to decrease selection bias and using blinding method to reduce information bias. However, it is difficult to be double-blinded in practice because both doctors and subjects can see and feel the difference between fire needle acupuncture and filiform needle acupuncture, especially Chinese people, who are particularly familiar with acupuncture and moxibustion. Therefore, only the third-party evaluator will be blinded in this study.

### Trial status

Recruitment began in November 2020 and will end in November 2021.

This protocol is the first version.

Date: January 8, 2020

## Data Availability

We will share the data after the trial is finished. The full data set will be available by an author contact when this trial is completed and published.

## Abbreviations

TCM: Traditional Chinese medicine
WOMAC: Western Ontario and McMaster Universities Osteoarthritis Index
VAS: Visual analog scale
SF-12: 12-item Short Form Health Survey
ITT: Intention-to-treat
PP: Per-protocol population
